### Study population

All people with T1D, and people with pancreatogenic or Type 3c diabetes who meet the public funding access criteria for an insulin pump and CGM [34], will be eligible to participate. Speed of access will be based on their prioritisation score. Furthermore, interested people must have a suitable health care team (determined by study clinical staff) who are available and willing to provide ongoing care to the person with diabetes once their participation in the study is complete. Existing healthcare teams will be notified when their patient has been enrolled and updated throughout their time enrolled in the Hub. Individuals who are pregnant will not be eligible to participate as these individuals will be prioritised through existing health delivery pathways. Additionally, those who have non-diabetes related, active moderate-to-severe health and/or mental health issues, will be referred to appropriate health care providers first for support and management, before transitioning to diabetes technology (at the discretion of the clinical team). In situations where additional requirements are identified, eligibility will be assessed on a case-by-case basis to ensure safety and support of transitioning to AID (for example, severely impaired vision or recent acute medical event).

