### Statistical analysis

Pharmac, NZs pharmaceutical funding agency, estimates there are 18,000 to 21,000 people with pancreatic insufficiency (mostly T1D) living in NZ who would be eligible for funded CGM [11], of whom 85–90% were not using AID in 2023. We believe the Hub will facilitate approximately 500 new AID starts per year (provided by 2.4 full time equivalent clinical staff, per year).

A sample size of 500 or more participants will provide > 90% power, with a two-sided alpha of 0.05, to detect small changes in continuous outcomes (effect sizes ≥ 0.15) and estimate binary outcomes to within +/- 5%.

Numbers of people referred to the Hub, enrolled, and started on AID will be tabulated by the key demographic and clinical variables required for calculation of the prioritisation score as listed under Sect. 2.5.1.

Incidence proportions, stratified by region and priority subpopulations, will be calculated as the number of AID starts divided by the number of eligible people not on AID as estimated from national administrative datasets. For comparisons with other providers, an individual will be considered to have started on AID on the date they are first dispensed a subsidised pump as recorded by Health New Zealand.

Interrupted time series analysis will be used to investigate the impact that the Hub has on the rate of new AID starts nationally, and by region, Absolute numbers and incidence proportions of new AID starts will be calculated for consecutive time periods and displayed graphically. Generalised linear (Poisson) regression models will be used to estimate changes in the in the numbers and incidence of new AID starts before versus after deployment of the Hub. Differences between regions, such as workforce capacity, may be explored in models to identify facilitators and barriers to AID uptake.

Intervention effectiveness will be confirmed by descriptively summarising changes in Hub participants’ HbA1c and CGM metrics before versus after starting on AID.

National laboratory and CGM data is not available for those not enrolled in the study.

Incidence rates of adverse events will be calculated for study participants after AID start and compared to control populations utilising generalised linear regression models, adjusting for demographic factors (age, gender, ethnicity, NZ deprivation index). Controls will included study participants prior to AID start and non-study people with type one diabetes who have and have not started on AID.

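### The safety comparison with non-study controls is not like with like: Hub entry rules and prioritisation select participants, and the model adjusts only for demographics

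*Protocol article*

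**What the plan says.** The Statistical analysis section of the protocol article compares adverse-event incidence after AID start with control populations, using generalised linear models. It names the controls: "Controls will included study participants prior to AID start", and "non-study people with type one diabetes who have and have not started on AID". The stated adjustment is "adjusting for demographic factors (age, gender, ethnicity, NZ deprivation index". No other covariate, matching or eligibility restriction is given for these controls. The Intervention safety section lists the events (death and hospital admission for DKA, severe hypoglycaemia and hyperglycaemia) and says control data come from national records.

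The Study population section sets Hub entry:
- "Individuals who are pregnant will not be eligible to participate as these individuals will be prioritised through existing health delivery pathways".
- People with "non-diabetes related, active moderate-to-severe health and/or mental health issues, will be referred to appropriate health care providers first", at the clinical team's discretion.
- Where further needs are identified, "eligibility will be assessed on a case-by-case basis to ensure safety and support of transitioning to AID"; a recent acute medical event is one of the examples given.
- People with pancreatogenic or Type 3c diabetes who meet the funding criteria are admitted alongside people with T1D.

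Table 2 (Prioritisation score) then gives points for raised HbA1c, severe hypoglycaemia in the last two years and known complications, among other items. Invitations depend on this score and on study capacity.

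**The concern.** The entry rules and the prioritisation score both act on characteristics plausibly related to the safety events. Someone with T1D whom the Hub declines, or has deferred, is a non-study person with T1D and so fits the control description as written. Pregnant people are sent to existing services, which may place them among the non-study AID users. None of the four demographic covariates measures pregnancy, comorbidity, recent acute illness, diabetes type or prior glycaemic risk.

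The safety of the Hub is part of the first objective, although safety is a secondary outcome. An adjusted rate ratio against national controls will be read as evidence about the Hub. As specified, it mixes any effect of the Hub with differences in who was let in and who was invited first. Participants' pre-AID period cannot stand in for the external comparison on death, because every participant was alive at AID start.

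**Working it through.** **1. The plan's own figures.** With N = 500 and a standardised change of 0.15, power is Φ(0.15 × √500 − 1.96) = Φ(1.394) = 91.8%. The 95% half-width for a proportion is at most 1.96 × √(0.25/500) = 4.4%. Both reproduce the stated >90% and ±5%. They concern changes within participants and single proportions, and say nothing about the safety rate ratio. The document gives no event rate or rate ratio for safety.

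**2. The groups side by side.**

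| Feature | Hub participants | Non-study controls as described | In the model? |
|---|---|---|---|
| Pregnancy | Not eligible | No restriction stated | No |
| Active moderate-to-severe non-diabetes illness | Deferred at discretion | No restriction stated | No |
| Recent acute medical event | Case by case | No restriction stated | No |
| Diabetes type | T1D and Type 3c | T1D only | No |
| High HbA1c, complications, severe hypoglycaemia | Prioritised | Not prioritised | No |
| Age, gender, ethnicity, deprivation | – | – | Yes |

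Diabetes type differs from the other entry rules: the Hub group is the broader one, and every T1D control satisfies the Hub's rule.

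**3. Entry rules alone.** Assume a true rate ratio of 1. Let f be the share of controls who would not pass Hub entry, and k their event rate relative to the other controls. Both are assumptions. The expected Hub/control ratio is 1/(1 − f + f·k).

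| f | k | Expected ratio |
|---|---|---|
| 2% | 2 | 1/1.02 = 0.98 |
| 5% | 2 | 1/1.05 = 0.95 |
| 5% | 3 | 1/1.10 = 0.91 |
| 10% | 3 | 1/1.20 = 0.83 |
| 20% | 3 | 1/1.40 = 0.71 |

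Applying the same rules to the controls sets f = 0 and returns 1.00.

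**4. Prioritisation alone.** Assume 50% of Hub participants and 20% of controls are clinically high-risk, with twice the event rate. The ratio is (0.5 + 0.5 × 2)/(0.8 + 0.2 × 2) = 1.5/1.2 = 1.25. With 40% against 20% it is 1.4/1.2 = 1.17.

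**5. Both together**, taking the effects as multiplicative and 1.25 for prioritisation:
- f = 5%, k = 2: 1.25/1.05 = 1.19
- f = 10%, k = 3: 1.25/1.20 = 1.04
- f = 20%, k = 3: 1.25/1.40 = 0.89

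With no true difference, the ratio falls on either side of 1 depending on inputs that the documents do not supply.

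**The case against.** The strongest reply is that one sentence naming the control populations does not say they are unrestricted, and that code-level filters usually sit in a full protocol or SAP. In part this stands: a filter may exist elsewhere. But the article fixes both the control populations and the adjustment set. By contrast, it states an eligibility restriction for the AID-start incidence denominators and a matched control group for the Cost-effectiveness analysis. The safety controls have neither.

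Other parts of the reply do stand and limit the point:
- Participants' pre-AID period is already a planned comparator made up of people who passed the same entry rules.
- Non-study AID users have already been selected by a provider, so the entry-rule mismatch probably weighs most on controls not using AID.
- The illness rule is a discretionary deferral, so those people may enrol later, and it can be only partly reproduced from administrative codes.
- The illness rule concerns non-diabetes conditions, while the named events other than death are diabetes admissions. Large values of k are therefore hard to defend.

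A reader might infer that the Hub will look safer than it is, because sicker people remain among the controls. The documents do not support that direction: the prioritisation score selects for diabetes-related risk and pushes the ratio the other way. Nor do they support saying that controls fail the Hub's diabetes-type rule.

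**Conclusion.** The point holds as one of non-comparability. As written, the external-control comparison sets a group selected by eligibility and clinical priority against people with T1D to whom neither selection is applied, and adjusts for demographics only. The direction and size of the net bias cannot be determined from the documents. The ratios above illustrate that the sign is open; they do not estimate the bias, and they rest wholly on assumed values of f, k and the high-risk shares. The eligibility mismatch does not affect the comparison with participants' own pre-AID period. Because this is a secondary outcome and the remedy is cheap, it is a worthwhile improvement rather than a flaw that undermines the study.

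**What to change.** Amend the safety paragraph of the Statistical analysis section, for the external-control comparison only:

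1. Limit it to people with T1D on both sides, and describe Type 3c participants separately.
2. Give each non-study control an index date. For AID users, the plan's own start definition (first dispensing of a subsidised pump) can serve; for people not on AID, a date must be assigned. From that date, apply the Hub entry rules that national data can code: at least pregnancy, and recent acute or mental-health admission where available.
3. Add prior-year admissions for DKA, for severe hypoglycaemia and for any cause as covariates alongside the demographic factors. Leave them out of the participant pre/post comparison, where the first two are the outcome.
4. State as residual limitations the discretionary criteria that cannot be coded, and HbA1c, which the section says is unavailable nationally for people not enrolled.

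This changes analysis wording and adds filters to the kind of national admission data the plan already uses. Recruitment, eligibility and care are untouched. The price is a smaller control set and imperfect proxies, and whether national data can supply each proxy must be confirmed.

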## Discussion

Despite evidence supporting AID as the gold standard in managing T1D, structural and systemic barriers continue to limit access [29, 32], especially for Indigenous peoples [5, 6, 43], and those living in rural areas [31]. This study leverages our research groups specialist knowledge in advanced diabetes technology to propose a solution to an identified problem in the current diabetes health care provision. By decentralising training and support, this novel remote Hub aims to overcome workforce capacity limitations and methodological and geographical barriers. This is the first study to work in partnership with the National health care provider to implement an new model of care specific to AID. Overall this study aims to impact individuals and health care systems so that people living with diabetes, and diabetes care providers accross AoNZ experience signficant benefits from this new model of care.

Ultimately, the primary beneficiaries of this study will be people with diabetes, who should receive expedited access to the anticipated health improvements facilitated by AID, as well as reduced diabetes-related burden of care through automation of up to 50–75% of insulin dosing [1, 44]. Staff in diabetes care teams will also experience gains in training and support, which we hope enables clinical practice dissemination in the existing healthcare system. Furthermore, we anticipate that this new model of care will be cost-effective and help to reduce the long term economic burden to the NZ health system.

A key strength of this study is the focus on equitable access by prioritising people who have an elevated HbA1c, are of Māori or Pacific ethnicity, live rurally, have an occupational requirement, are younger than 25 years old, have diabetes-related complications and/or have history of severe hypoglycaemia, using the prioritisation score developed the study team. Furthermore this study provides nutrition support to participants who require additional education in this area, but without delaying AID start.

This study addresses an urgent and growing health need in NZ, and provides a framework for the roll out of a sustainable and equitable model of care that complements existing services. We view this as the future of mainstream diabetes technology training and support, especially during this period of peak uptake. Establishing a precedent and evidence for this sort of nationally delivered health care model is vital for NZ, and this work could be adapted for management of other chronic conditions.

## Data Availability

No datasets were generated or analysed during the current study.
